#### Usual care

Participants assigned to the UC group (i.e., UC participants) will proceed through the preoperative weight management program provided by the center. The login credential for each UC participant will, however, provide access to a secure website to complete data collection (i.e., a survey battery and physical activity monitoring) at W1, W2, and W3. UC participants will have the opportunity to receive up to $30 worth of Amazon electronic gift cards, which is similar to previous research [36, 37]. Specifically, UC participants will receive $10 for completing the W1 survey battery and W1 physical activity monitoring, $10 for completing the W2 survey battery and W2 physical activity monitoring, and $10 for completing the W3 survey battery and W3 physical activity monitoring. UC participants will be given 4 weeks of 24 h access to the FFW online intervention approximately 1 month after data collection for this study is closed.

#### Fun For Wellness

Participants assigned to the FFW group (i.e., FFW participants) will proceed through the preoperative program provided by the center and will be given 4 weeks of 24 h access to the FFW online intervention during data collection for this study. The login credential for each FFW participant will provide access to both the FFW intervention and to a secure website to complete data collection at W1, W2, and W3. FFW participants will have the opportunity to receive a total of up to $45 worth of Amazon electronic gift cards, which is similar to previous research [36, 37]. Specifically, FFW participants will receive $10 for completing the W1 survey battery and W1 physical activity monitoring; $25 for completing the W2 survey battery, W2 physical activity monitoring, and at least 30 post-introductory BET I CAN challenges; and $10 for completing the W3 survey battery and W3 physical activity monitoring. The remuneration plan at W2 is linked to completing post-introductory BET I CAN challenges to encourage compliance with the FFW intervention as suggested in previous research [36, 37].

#### BET I CAN challenges

Self-efficacy theory [8] provided the theoretical framework that guided the creation of capability-enhancing learning opportunities (i.e., BET I CAN challenges) for FFW participants to engage with. The capability-enhancing learning opportunities provided to participants come in the form of 152 interactive and scenario-based challenges organized in the online environment by the BET I CAN acronym [36]. The *b*ehavior-focused challenges are intended to increase a participant’s capabilities to set a goal and to create positive habits [49]. The *e*motion-focused challenges are intended to increase a participant’s capabilities to cope with negative emotions and to cultivate positive emotions [50]. The *t*hought-focused challenges are intended to increase a participant’s capabilities to challenge negative assumptions and to create a new narrative for their life [51]. The *i*nteraction-focused challenges are intended to increase a participant’s capabilities to communicate and connect with others [52]. The *c*ontext-focused challenges are intended to increase a participant’s capabilities to read cues and to change cues in the environment [53]. The *a*wareness-focused challenges are intended to increase a participant’s capabilities to know herself/himself and to know the issue [54]. The *n*ext step-focused challenges are intended to increase a participant’s capabilities to make a plan and to stick with a plan [55]. In summary, the BET I CAN challenges in the FFW intervention provide opportunities for a participant to increase his or her capabilities to organize and execute actions that may increase their well-being and physical activity [36, 37].

### Data collection

#### Study timeline

Three waves of data will be collected over a 13-week period (see Fig. 3), which is similar to both the 2015 FFW efficacy trial [36] and the 2018 FFW effectiveness trial [37]. Data collection at W1 will include the W1 survey battery and W1 physical activity monitoring. The W1 survey battery will be completed in week 1. The W1 physical activity monitoring will be completed in week 2. Participants will return physical activity monitoring items (to be detailed in the physical activity monitoring section) to the research staff in week 3. The intervention will be delivered in week 3 through week 6. Data collection at W2 will include the W2 survey battery and W2 physical activity monitoring. The W2 survey battery will be completed in week 7. The W2 physical activity monitoring will be completed in week 8. Participants will return physical activity monitoring items to the research staff in week 9. Data collection at W3 will include the W3 survey battery and W3 physical activity monitoring. The W3 survey battery will be completed in week 11. The W3 physical activity monitoring will be completed in week 12. Participants will return physical activity monitoring items to the research staff in week 13. The timeline for this study is similar to timelines used in other physical activity interventions in adults with obesity [6, 32, 33].

#### W1, W2, and W3 physical activity monitoring

Instruments designed to measure physical activity and the acceptability and feasibility of accelerometer-based assessment of physical activity will be included in the PAMP. Research staff will prepare and send the PAMP to each participant via regular USA mail approximately 1 week before physical activity monitoring is scheduled to occur. A commercial-grade (Fitbit Zip) and a research-grade (Actigraph wGT3X-BT) accelerometer will be initialized and attached to an adjustable nylon belt to measure physical activity objectively. The order of the two monitors (i.e., which monitor is medial or lateral) will be randomized to account for small differences by wear location. The same two monitors will be provided to each participant at each time point to limit inter-monitor variability. Throughout the study duration, no app, firmware, or software updates will be allowed and one laptop computer will be used for all monitors, to ensure consistent clock times for data analysis. The primary measure of physical activity in this study will be the average minutes per day of MVPA based on both widely accepted recommendations for health-enhancing physical activity [3, 4] and the particular physical activity emphasis manifest in the FFW intervention [37].

Consistent with previous research [34], a brief cover letter, written and pictorial wear instructions, a daily log sheet regarding wear time, protocol checklist, and one preaddressed postage-paid, padded, return envelope (regular USA mail) will be included in the PAMP. In the cover letter, participants will also be directed to use their login credential to access electronic copies of the paper-based documents in the PAMP. Wear instructions will include the following: ensure that the belt is snug around the waist and that monitors are placed over the right hipbone crest at the anterior axillary line during wear time; begin to wear the monitors upon awakening the day after receipt for a seven-day interval; remove the monitors when sleeping or during water intensive activities (e.g., swimming, bathing) and reattach the monitors upon awakening or at cessation of water intensive activities; complete the daily log sheet online with date and time the monitors are put on and taken off each day; and return the monitors and belt on the day after a 7-day interval via the preaddressed postage-paid, padded, return envelope provided. On the day after a 7-day interval, participants will receive a reminder by e-mail and/or phone to return the belt and the monitors. At this time, participants will also be prompted to complete instruments designed to measure the acceptability of accelerometer-based assessment of physical activity and self-reported physical activity.

Upon return of the belt and the monitors the research team will follow a protocol based on previous research [34]. Data will be downloaded using a standard universal serial bus port. Belts will be laundered. Batteries in the monitors will be charged or changed if necessary. Monitors will be reinitialized for use. Within a few weeks of the return of the monitors, participants who provide usable data (to be described in the section on the ActiGraph wGT3X-BT) will be e-mailed (or mailed via regular mail if an e-mail address is unavailable) a preliminary estimate of their wear time and average minutes per day of MVPA in relation to broad categories of recommended MVPA per week (i.e., 0–4.21 min/day = minimal; 4.21–21.36 min/day = less than recommended; ≥ 21.36 min/day = meeting recommendation of 150 min/week). Participants who do not provide usable data will be informed that their average minutes per day of MVPA cannot be estimated due to insufficient data.

#### Fitbit Zip

The Fitbit Zip (San Francisco, CA, USA) is a tri-axial commercial-grade accelerometer that will be used to measure physical activity objectively. There is evidence for the validity of physical activity measures produced by the Fitbit Zip in both treadmill-based [31, 56] and free-living [31] activities in adults. Average minutes per day of MVPA will be determined using the Fitbit application, which uses a proprietary algorithm to estimate *fairly active minutes* and *very active minutes*, consistent with previous research [47, 48].

The cost of a Fitbit Zip is approximately 60 USA dollars. The Fitbit Zip can store data up to 7 days and sync wirelessly with the Fitbit mobile application up to a 20-ft range. A Fitbit website account will be established for each Fitbit Zip, but a participant will not be able to access the account [47]. The default settings of the Fitbit Zip (e.g., goals) will be removed because these settings may be inappropriate for adults with obesity [57]. Removing these settings also reduces the likelihood of confounding effects from behavior change techniques built into activity monitors [58]. The only physical activity display that a participant will be able to view while wearing this device will be the number of steps taken because this information cannot be programmed to be hidden.

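### The Fitbit Zip's stated 7-day storage does not cover 7 wear days plus return by mail, so the Aim 2 comparisons involving the Zip may rest on different days

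*Protocol article*

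**What the plan says.** On the device (Protocol article, Fitbit Zip): "The Fitbit Zip can store data up to 7 days and sync wirelessly with the Fitbit mobile application up to a 20-ft range". In the same section: "A Fitbit website account will be established for each Fitbit Zip, but a participant will not be able to access the account".

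On the schedule (W1, W2, and W3 physical activity monitoring):
- The package goes out "via regular USA mail approximately 1 week before physical activity monitoring is scheduled to occur", with the monitors already initialised.
- Participants are to "begin to wear the monitors upon awakening the day after receipt for a seven-day interval" and then "return the monitors and belt on the day after a 7-day interval via the preaddressed postage-paid, padded, return envelope provided".
- The return route is ordinary post: "one preaddressed postage-paid, padded, return envelope (regular USA mail) will be included in the PAMP".
- Processing starts afterwards: "Upon return of the belt and the monitors the research team will follow a protocol based on previous research". Data download is one of the steps listed there.
- A single laptop serves all monitors.

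The ActiGraph wGT3X-BT section gives that device up to 43 days of storage. It also sets the usable-data rule: at least 4 days, one of them a weekend day, each with at least 10 hours of wear.

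Aim 2 compares mean daily MVPA from the ActiGraph, the Zip and the IPAQ at each wave. Pearson's r is red below .60 and green from .70. The Bland-Altman light depends on the share of observations beyond the mean difference ± 2 SD.

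**The concern.** Two monitors on one belt should measure the same week. On the stated figures only one of them can hold that week until it is read. If the Zip mean is taken over what is left in memory, while the ActiGraph mean covers all valid days, part of any disagreement comes from comparing different days and not from the devices.

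Aim 2 is where the study decides whether accelerometry should be used within the intervention, and Aim 3 assumes a positive answer. Two of the three pairings in Aim 2 involve the Zip. The IPAQ asks about the previous week and is prompted on the day after the wear interval, so it too spans the worn week while the Zip may not. The procedure repeats at all three waves, and days lost from device memory cannot be recovered later.

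**Working it through.** **Inputs from the article:** Zip capacity 7 days; wear on days 1 to 7 (first wear day = day 1); posting on day 8; ActiGraph capacity 43 days; usable-data minimum 4 days.

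**Assumed, because not stated:** return transit of t days; the gap of k days between initialisation and first wear; what the Zip does when its memory is full.

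**Step 1, day of reading.** The Zip is read on day 8 + t. With any transit (t ≥ 1) that is day 9 or later, against 7 days of storage.

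**Step 2, memory overwrites the oldest data.** If the read day counts as one of the seven, days 2 + t to 8 + t are held, which leaves 6 − t wear days. If only the seven full days before reading are held, days 1 + t to 7 + t remain, which leaves 7 − t.

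| t (days in mail) | Wear days left of 7 (6 − t to 7 − t) |
|---|---|
| 1 | 5 to 6 |
| 2 | 4 to 5 |
| 3 | 3 to 4 |
| 4 | 2 to 3 |
| 5 | 1 to 2 |

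The days lost are the earliest. The count falls below the 4-day minimum from t = 3 or t = 4, depending on the counting.

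**Step 3, memory stops when full.** Recording covers the first 7 days from initialisation, so 7 − k wear days are held: days 1 to 6 at k = 1, days 1 to 4 at k = 3, none at k = 7. The days lost are the latest.

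**Step 4, ActiGraph.** Even with 8 days before wear and 7 days of return transit it needs 8 + 7 + 1 + 7 = 23 days, within 43. It keeps all seven wear days.

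**Step 5, effect on r (illustration).** Let B and W be the between-person and day-to-day variances of Zip MVPA, with B + W = 1, so that B is the day-to-day intraclass correlation. If days are exchangeable, replacing the 7-day Zip mean by a mean over m of those days leaves its covariance with the other measure unchanged and raises its variance from B + W/7 to B + W/m. So r is multiplied by √[(B + W/7)/(B + W/m)]. B = 0.3 to 0.5 and a full-week r of 0.75 are assumptions.

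| m | Factor at B = 0.3 | Factor at B = 0.5 | r, from 0.75 |
|---|---|---|---|
| 5 | √(0.400/0.440) = 0.95 | √(0.571/0.600) = 0.98 | 0.72 to 0.73 |
| 4 | √(0.400/0.475) = 0.92 | √(0.571/0.625) = 0.96 | 0.69 to 0.72 |
| 3 | √(0.400/0.533) = 0.87 | √(0.571/0.667) = 0.93 | 0.65 to 0.69 |

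With 5 days left this r stays green. With 4 it lies on the boundary, and with 3 it turns yellow although the devices agree as well as before.

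**The case against.** The strongest reply is that the article does not say when the Zip is synced. Its download step mentions a USB port, while the Zip is described as syncing wirelessly. It points to earlier studies for the handling procedure, and an interim sync could stand in the full protocol. The article also does not say whether the 7-day limit applies to the daily active-minute totals that the analysis uses. All of this stands, and it is why the conclusion is that days may be lost. It does not remove the conflict: the sequence that the article does set out runs longer than the capacity it states.

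Four stronger readings are tempting and are not supported:
- *The first wear days are certainly gone.* That needs overwriting memory. If recording stops when full, the last days go.
- *A full week of memory is used up before wear starts.* Wear begins the day after receipt and the initialisation date is not given, so the gap may be shorter than a week.
- *Days in the mail enter the Fitbit mean at near-zero activity.* Nothing says so. The daily log and the shared belt identify the wear days for both monitors.
- *False bias drives the Bland-Altman light.* The light is set relative to the sample's own mean and SD and expressly not by a hypothesis test, so a constant shift does not move it.

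The ActiGraph-IPAQ comparison and the ActiGraph-based participation and retention rates are not affected.

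**Conclusion.** The point holds as a mismatch between stated figures. Seven days of Zip storage do not cover the interval from first wear to reading, which is 8 days plus transit, and no interim sync is described. The Zip and the measures it is compared with may therefore cover different days.

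The size depends on transit time and memory behaviour, neither of which is given. With overwriting, 4 to 5 of 7 wear days remain at 2 days of transit and 3 to 4 at 3 days. The main consequence is noise, which lowers r. On the assumptions used above, that can cost a borderline result one light but does not by itself produce a red one at these transit times. Systematic bias would need the lost days to differ from those kept, which the article gives no ground to assume.

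This should be fixed before the first package is mailed. It touches two pairings within one aim of a 30-person pilot and does not undermine the rest of the study.

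**What to change.** Reconcile the sections on monitoring, the Fitbit Zip and the ActiGraph with the Aim 2 analysis.

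1. **Shared-day rule.** For Aim 2, compute Zip and ActiGraph MVPA over the same calendar days: days confirmed by the log, valid on the ActiGraph (at least 10 hours) and still present on the Zip. Require at least 4 shared days and otherwise treat the pair as missing. This costs one sentence in the analysis plan and some lost pairs. From Step 2, all pairs could be lost once transit reaches 3 or 4 days, so the rule is not enough alone. Nor does it repair the Zip-IPAQ pair, because the IPAQ reports on the whole week.

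2. **Bench test.** Before launch, send one initialised Zip through the full mailing cycle and record which days can be read on return. If wear days are lost, use faster return postage with sync on receipt. The cost is one trial mailing and, if needed, somewhat higher postage for about 30 packages per wave.

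A background sync in the participant's home would also preserve the data. It is harder than it looks, given the 20-ft range, the account that participants may not access and the single study laptop.

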#### ActiGraph wGT3X-BT

The ActiGraph wGT3X-BT (Pensacola, FL, USA) is a tri-axial research-grade accelerometer that will be used to measure physical activity objectively. ActiGraph devices have been used extensively as a reference (e.g., gold-standard) device to measure free-living physical activity objectively in adults [29]. Monitors will be initialized to collect raw acceleration data at 30 Hz using ActiLife software (version 6.13.3). Upon download, data will be re-integrated to 60-s epochs, and non-wear time will be defined as ≥ 90 continuous minutes of zero counts, with allowance for 2 min of acceleration that are preceded and followed by at least 30 min of continuous zeros [59]. Usable data will be defined as follows: (a) a log sheet with a valid start date is submitted, (b) a monitor is worn for at least 4 days (including one weekend day) with at least 10 h of valid wear time per day, and (c) no evidence of monitor error (e.g., activity counts > 20,000 or lengthy strings of repeated activity counts). Unusable data will be treated as missing data. Average minutes per day of MVPA will be calculated based on established cut points (e.g., > 1952 counts per minute) [60].

The cost of an ActiGraph wGT3X-BT is approximately 225 USA dollars. The ActiGraph wGT3X-BT can store data up to 43 days and sync wirelessly with the ActiLife mobile application; however, the wireless function will be disabled to maximize battery life. A participant will not be able to view any physical activity displays while wearing this device. The pairing of the ActiGraph wGT3X-BT with the Fitbit Zip is based on previous research where at least a moderately high correlation and a moderate level of agreement between measures of average minutes per day of MVPA produced by these two accelerometers has been observed [47, 48].

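### The Fitbit Zip's stated 7-day storage equals the wear period and leaves no room for return mail, so Fitbit wear days may be lost before download

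*Protocol article*

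**What the plan says.** The Fitbit Zip section gives the device's memory and sync range: "The Fitbit Zip can store data up to 7 days and sync wirelessly with the Fitbit mobile application up to a 20-ft range". It adds that each Zip has a website account but "a participant will not be able to access the account". MVPA for this device is taken from the Fitbit application's totals of fairly active and very active minutes.

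The section on W1, W2, and W3 physical activity monitoring sets the handling. Initialised monitors are mailed about 1 week before monitoring is due. Participants are told to "begin to wear the monitors upon awakening the day after receipt for a seven-day interval" and then to "return the monitors and belt on the day after a 7-day interval via the preaddressed postage-paid, padded, return envelope provided". On the return route, "one preaddressed postage-paid, padded, return envelope (regular USA mail) will be included in the PAMP". Data are downloaded once the belt and monitors are back with the research team, and "one laptop computer will be used for all monitors". No reading or sync of the Zip during the wear week is described.

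The Study timeline puts return in the week after wear at each wave. For W2, for example, wear is in week 8 and "Participants will return physical activity monitoring items to the research staff in week 9".

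The companion device on the same belt is not so limited: "The ActiGraph wGT3X-BT can store data up to 43 days".

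Aim 2 compares average minutes per day of MVPA from the ActiGraph, the Fitbit Zip and the IPAQ at each wave. The correlation light is red below .60 and green from .70. The article states no rule for matching days between the two accelerometers.

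**The concern.** Seven days of wear use all of the stated storage, and posting and mail time follow before anyone is described as reading the device. If the memory keeps the latest 7 days, each day in the post can displace a wear day. If it fills and then stops, the days between initialisation and first wear use it up from the other end. The ActiGraph keeps the full week in both cases, so Aim 2 could compare averages taken over different days.

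The part of Aim 2 at stake is the ActiGraph-Fitbit correlation, which bears on whether the lower-cost monitor is judged suitable. A weaker correlation could then partly reflect mail time. The loss could recur at all three waves in a study of 30 participants and could not be undone afterwards. Nor would an Aim 1 rate show it, because the participation and retention rates use the definition of usable data given in the ActiGraph section.

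**Working it through.** **Inputs from the protocol.** Fitbit storage 7 days; wear 7 days; posting on the day after; reading on return; ActiGraph storage 43 days; correlation cut-offs .60 and .70.

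**Assumptions, not in the protocol.** Mail time t, taken as 2 to 5 days. A memory that keeps the most recent 7 days. A single-day ICC for MVPA of 0.5 (range 0.3 to 0.7). A full-week ActiGraph-Fitbit correlation of .75.

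**Step 1: wear days left at reading.** Wear is on days 1 to 7, posting on day 8 and reading on day 8 + t. Days kept = max(0, 7 − t) if the reading day takes no slot, or max(0, 6 − t) if it does.

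| t | Read on day | Kept, reading day not counted | Kept, reading day counted |
|---|---|---|---|
| 0 | 8 | 7 | 6 |
| 1 | 9 | 6 | 5 |
| 2 | 10 | 5 | 4 |
| 3 | 11 | 4 | 3 |
| 4 | 12 | 3 | 2 |
| 5 | 13 | 2 | 1 |
| 6 | 14 | 1 | 0 |

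Holding all 7 wear days needs storage of 7 + t or 8 + t days. For t = 2 to 5 that is 9 to 12, or 10 to 13, against the stated 7.

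**Step 2: the other memory behaviour.** If recording stops when full and counts from initialisation, a gap of g days before wear leaves max(0, 7 − g) wear days: 4 for g = 3, and 0 for g = 7. The planned lead time is about 1 week.

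**Step 3: effect on the correlation.** Let the between-person and single-day variances both be 1 (ICC 0.5). The 7-day ActiGraph mean then has variance 1 + 1/7 = 1.143. Put the device error, variance e, on the Fitbit and let it not shrink with the number of days. With k of the 7 days left,

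r(k) = sqrt(1.143 / (1 + 1/k + e)).

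Setting r(7) = .75 gives e = 1.143 × (1/.5625 − 1) = 0.889. Then:

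- k = 5: sqrt(1.143/2.089) = .74
- k = 4: sqrt(1.143/2.139) = .73
- k = 3: sqrt(1.143/2.222) = .72
- k = 2: sqrt(1.143/2.389) = .69
- k = 1: sqrt(1.143/2.889) = .63

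The light stays green down to 3 days and is yellow at 2 or 1. None of these values is red.

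**Step 4: sensitivity.** A harsher model multiplies .75 by the correlation between a 7-day mean and the mean of k of those days, sqrt((ICC + (1 − ICC)/7) / (ICC + (1 − ICC)/k)).

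| ICC | k = 4 | k = 3 | k = 2 | k = 1 |
|---|---|---|---|---|
| 0.3 | .69 | .65 | .59 | .47 |
| 0.5 | .72 | .69 | .65 | .57 |
| 0.7 | .73 | .72 | .70 | .65 |

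Here red appears with 1 day left at ICC 0.5, and with 2 or 1 left at ICC 0.3.

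**Step 5: worst case.** If unworn transit days were averaged in as zero MVPA, the Fitbit mean would fall to k/7 of its value: 0.57 with 4 days and 0.29 with 2. The protocol does not say this will be done.

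**The case against.** The best defence is that loss is inferred and not stated. The article does not say what the Zip does when its memory is full, how long mail takes, or whether the 7-day limit covers the daily active-minute totals that form the outcome or only more detailed records. Barring participants from the website account does not by itself rule out a sync. The single laptop is justified by consistent clock times and sets no reading schedule. A sync procedure may stand in the full protocol. The daily log of on and off times would let staff identify unworn days, and missing dates could be noticed when the first belts come back.

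Most of this stands, and it limits the point to a possible loss. A reader might infer that wear days are certain to disappear, or that Aim 2 would be pushed to red. The documents support neither. The base calculation gives no red value, and the Bland-Altman light counts points beyond limits scaled to the SD of the differences themselves, so added noise mainly widens those limits. An effect on that light is not shown.

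What the defence does not remove is the mismatch in stated content. Storage, wear, posting and reading are all given, and they do not fit together without a step that the article does not describe. The USB download mentioned for the monitors does not help, since it also follows return. A common-date rule in an unseen analysis plan could align the two devices but could not recover lost days.

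**Conclusion.** The point holds as a risk. On the protocol's own figure the Zip has no storage margin beyond the wear week, so Fitbit wear days may be lost before download at every wave. Under a rolling memory and 2 to 5 days of mail, 5 to 2 wear days would remain, or 4 to 1 if the reading day counts. An assumed full-week correlation of .75 at ICC 0.5 would fall to about .73 to .63 with 4 to 1 days, which can turn a green light yellow. Red arises only with a harsher error model and very few days, with a low ICC, or if transit days are averaged in.

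The ActiGraph-based Aim 1 rates and the ActiGraph-IPAQ comparison are unaffected. This should be fixed before the first mail-out. Confidence is medium, because the mail time, the memory behaviour and the scope of the 7-day figure are not documented.

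**What to change.** 1. Before the first mail-out, send one initialised Zip out and back on the study timetable, with 7 days of wear. Check whether the fairly active and very active minutes for all 7 dates reach the application. If they do, correct or qualify the 7-day figure in the protocol.
2. If they do not, arrange a sync within the storage limit, or a faster return, without giving participants account access, and state when and by whom the Zip is synced. Under a rolling memory, faster return alone keeps all 7 days only if the device is read on day 8 and that day takes no slot; otherwise it only reduces the loss.
3. In either case, compute the ActiGraph-Fitbit correlation and agreement only on calendar dates recorded by both devices with a valid ActiGraph day. Report the number of Fitbit days recovered per wave.

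The cost is one test mailing, some sync or return logistics, a few lines of protocol and analysis text, and fewer days per pair where dates are missing. Replacing the monitor is not part of this low-cost fix: it would mean new devices and would give up the device pairing that the protocol justifies from earlier research.
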